## 2.4 Investigational products/intervention(s)

### 2.4.1 DNA

The DNA vaccine immunogens are encoded in plasmids derived from puC8 which contains genes for kanamycin resistance and containing the promoter sequence from CMV, the poly (A) signal from HPV-16 and the *E.coli* origin of replication. The plasmids cover subtypes A, B and C but there is evidence for extensive cross-reactivity at the level of both humoral and T cell responses in the recognition of HIV-1 Env and gag subtypes, broadening the geographical scope of such a multiclade vaccine (41), (42), (43). The 7 plasmids are pKCMVgp160A, pKCMVgp160B, pKCMVgp160C, pKCMVrevB, pKCMVp37A (AB), pKCMVp37B, and pKCMVRTB.

The primary envelope gene is that of subtype B. This gene was used for homologous recombination to obtain variable sites of subtypes A and C. Thus the most variable regions of gp120 from subtypes other than the primary could be included, and the most conserved proteins conserved in the vaccine mixture.

**Rev** of subtype B is included to augment the expression of the envelope genes. The vaccine also includes a plasmid encoding **RT** of subtype B, but does not include **pol**.

The pKCMVgp160B/A and pKCMV gp160B/C encode chimeric gp160B proteins with the hypervariable loops (V1-V5) exchanged for subtype A or C sequences, respectively.

The p37 gag subtypes A and B constructs encode the antigenically most relevant p17 matrix and p24 capsid proteins. p24 is the main vaccine target of the gag proteins and the exchange of p17 subtype A for the subtype B p17 will increase the response to conserved epitopes. The seven plasmids, expressing ten different HIV-1 genes, have previously been

injected at two distinct anatomical sites; with one pool containing the p37 (ABA and B) and RT genes and the other the gp160 (A, B and C) and rev genes. This was in order to minimise the chances of immunodominance causing interference between the immune responses to different components (44).

#### **2.4.2 MVA-CMDR Modified Vaccinia Ankara (MVA-CMDR)**

MVA-CMDR is a recombinant attenuated modified vaccinia virus-vector vaccine that has been genetically engineered to express HIV-1 gp150 (Subtype E, isolate CM235) and gag and pol (integrase-deleted and reverse transcriptase nonfunctional, Subtype A, isolate CM240) developed at the Laboratory of Viral Disease (LVD), that does not replicate in mammalian cells, National Institute of Allergy and Infectious Diseases (NIAID) by Bernard Moss and Patricia Earl. The vaccine preparation is formulated to contain  $10^8$  plaque forming units (pfu)/mL in sterile PBS (without  $\text{Ca}^{2+}$  and  $\text{Mg}^{2+}$ ), 7.5% lactose, pH 7.4. The vaccine is filled in 2 mL glass vials in a volume of 1.2 mL ( $10^8$  pfu/mL) or 0.4 mL ( $10^9$  pfu/mL). The vials are stoppered with grey butyl rubber stoppers and sealed with aluminum crimp seals. Storage of the MVA-CMDR vaccine is at  $-80^\circ\text{C}$  ( $\pm 10^\circ\text{C}$ ). The use of live attenuated Modified Vaccinia Ankara virus recombinants as expression vectors for heterologous HIV gene inserts has been shown in clinical trials to be safe and immunogenic (45-46). In particular, Modified Vaccinia Ankara (MVA)-based recombinants have been shown to induce antibodies and specific cellular immune responses mediated by CTLs. The Walter Reed Army Institute of Research/National Institutes of Health (WRAIR/INS) have produced a live recombinant poxvirus vector, MVA-CMDR, that is genetically engineered to express the following HIV genes: gp150 (Subtype E, CM235), gag, and pol (integrase-deleted and reverse transcriptase nonfunctional, Subtype A, CM240). This live attenuated vector vaccine candidate has been shown to be safe and immunogenic in two Phase I protocols, either administered alone (RV158 US, Thailand, WRAIR Protocol # 1143) or when used in a DNA prime/MVA boost immunisation strategy (47) including results from our own group from the phase I HIVIS01/02 study conducted in Sweden (48) and the phase II HIVIS03 study conducted in Dar es Salaam.

Several preclinical studies to evaluate the bio distribution of DNA vaccines (42) and MVA (Investigator's brochure, Edition 6, 6th December 2012) were performed in Sweden and in the United States and showed that DNA plasmids and MVA are quickly eliminated from different organs including the gonads. In further clinical trials of HIV vaccines conducted in Tanzania, using the same combination of vaccines, no adverse events were recorded in children of vaccinated mothers who became pregnant during the course of the study. However, in order to minimise the risk to the unborn child, all participants will be advised to avoid pregnancy (or pregnancy in partners) until 3 months after the last vaccination and contraception will be available at no cost. Verbal assurance is sought at the time of randomisation to confirm that pregnancy will be avoided until 3 months after the last vaccination.

#### **2.4.3 CN54rgp140/GLA-AF**

**CN54rgp140:** this is a recombinant C-clade Env protein, derived from a Chinese viral isolate. The C-clade HIV subtype is believed to cause more than 50% of worldwide HIV-1 infections, and is predominant in southern and eastern Africa and India. It comprises a sequence of 670 amino acids, and has been shown to be immunogenic in non-human primates and other animal models. CN54rgp140 has been manufactured (GMP) using a mammalian cell expression system by Polymun and purchased by Imperial College London.

**GLA-AF:** GLA is a synthetic lipid A adjuvant formulated in aqueous solution, manufactured to US GMP by IDRI and purchased by Imperial College. GLA-AF is an aqueous adjuvant formulation containing glucopyranosyl lipid A, a completely synthetic monophosphoryl lipid A (MPL®) like molecule. MPL is an adjuvant component of human vaccines licensed

worldwide. Both GLA and MPL adjuvants are potent stimulators of the innate immune system, specifically mobilizing antigen presenting cells through their binding and activation of the toll-like receptor 4 (TLR4).

To date, there have been three human clinical trials of the recombinant protein CN54 rgp140, known as MucoVac 1 (EudraCT number 2007-000781-20), MucoVac 2 (EudraCT number) and the TaMoVac 01 v4.0 amendment. The MucoVac trials were carried out at two sites in the UK (London and York). Fifty three healthy women have received three immunizations with CN54rgp140 adjuvanted with GLA-AF via one or more of the following routes: intramuscular, intranasal and intravaginal. Adverse events were mainly mild, and there were no serious or severe adverse events related to the vaccine products.

Further data supporting the safety of CN54 rgp140 and GLA-AF comes from similar recombinant envelope proteins and MPL respectively. Recombinant HIV envelope proteins have been extensively studied in large scale efficacy trials including the VaxGen and RV144 trials in which over 10,000 individuals have been exposed. MPL is an active ingredient in GlaxoSmithKline's propriety adjuvant AS04, which is in Cervarix, a licensed vaccine to prevent certain types of human papilloma virus infection associated with cervical cancer. Cervarix is licensed for use in the European Union and contains 50µg MPL. Pre-clinical studies suggest that the potency of GLA-AF is 10 fold greater than MPL, which would imply that the equivalent dose to 50µg MPL is 5µg GLA-AF. GLA has also been formulated in oil and water emulsion (GLA-SE) and this has been used in one previous clinical trial. Four of the first cohort of 8 volunteers received one IM immunisation with fluzone plus GLA-SE 5µg formulated in the emulsion. Three of the four experienced multiple grade 2 or higher adverse events, mainly local reactions but also headache and malaise, considered to be dose limiting toxicity and attributed to the emulsion formulation, so the dose ranging study in 84 individuals proceeded with a maximum dose of 2.5µg GLA-SE. None of the reported events in the 54 individuals that received up to 2.5µg GLA-SE reached dose limiting toxicity, and the proportion with grade 2 or higher events was similar in those receiving GLA-SE to those receiving emulsion without GLA: 30% and 25% respectively. There was one severe event considered related to vaccine in the GLA-SE groups, a headache that started on the day of immunization lasting 24 hours occurring in a participant that received 2.5µg GLA-SE. Priming the immune system prior to administration of GLA-AF did not alter the adverse event profile of CN54 rgp140/GLA-AF in TaMoVac 01. This was expected because GLA-AF does not stimulate adaptive immune responses that could lead to a cascade of cytokines and enhanced reactogenicity.

#### **2.4.4 Vaccine Delivery**

##### **2.4.4.1 Zetajet® Needle-Free Injection System**

The Zetajet® uses sterile, single-use syringes that deliver the study material ID which is self powered by a spring. The syringes will be prepared by the pharmacist and delivered to the clinic for vaccination upon request (see section 6). The syringes will be loaded into the Zetajet by the trained pharmacists, study doctor or nurse according to manufacturer's instructions. The Zetajet will be applied on the disinfected skin with light pressure. The study agent is expelled under pressure through a micro-orifice at high velocity in a fraction of a second. The Zetajet® device will be provided by Bioject Medical Technologies, Inc., [name].

##### **2.4.4.2 Derma Vax™ DNA Vaccine Skin Delivery EP**

The Derma Vax™ DNA Electroporation System is a device that delivers a tightly controlled and documented series of electrical pulses to the skin between two arrays of 2 mm long needles 4mm apart (see section 6).

##### **2.4.4.3 MVA-CMDR**

The CMDR-MVA/Placebo boost injection will be delivered IM in the deltoid muscle of the left arm according to standardised operational procedures.

#### 2.4.4.4 CN54rgp140/GLA-AF

100µg CN54rgp140 will be formulated with 5µg GLA-AF in aqueous solution by the pharmacist in the 2 hours prior to use and administered IM into the deltoid muscle of the right arm.

#### 2.4.5 Rationale for doses

The rationale for dose selection is based on previous HIVIS trials and the TaMoVac I trial. Results from the TaMoVac I did not show major differences between DNA vaccine deliveries of separate versus combined plasmid pools as well as between the higher and lower DNA doses. Therefore, the TaMoVac II will further investigate the lower TaMoVac I DNA dose (600 µg) with combined plasmid pools in a clinically more feasible (two shots) and less costly, dose sparing DNA vaccine concept (Group I). In addition the effect of electroporation will be investigated for the 600µg DNA dose (Group II) with the hypothesis to induce higher DNA vaccine efficacy in terms of immunological correlates. Furthermore, the options to decrease immunisation shots necessary to deliver the full dose will be evaluated by comparing administration of the DNA vaccine in one shot at a higher concentration of 6 mg/ml (Group III) as compared to previously used 2 shots at a concentration of 3 mg/ml as applied in Groups I and II. The CMDR-MVA and the CN54rgp140/GLA-AF doses are adapted from the previous HIVIS and TaMoVac I trials.

#### 2.4.6 Risks and benefits

The DNA and MVA immunogens have been well tolerated in the HIVIS 01, HIVIS 03 and TaMoVac I studies and have now been given to a total of ~260 participants in several settings. Injection with Zetajet is associated with the same level of discomfort as traditional injections. Electroporation with the ID Derma Vax™ device is associated with a momentary unpleasant contraction of superficial muscles, but very little pain. The effect subsides immediately. There is no indication that the increased delivery of DNA is associated with integration that could be clinically relevant. Bloodletting can be unpleasant and result in bruises that resolve within days. Participation in a study offers regular medical checkups and intense counselling to avoid sexually transmitted infections and pregnancies. Results from the study may contribute significantly to the development of an HIV vaccine.

→ ***Additional background information on HIV immune responses, HIV vaccine developments and vaccine delivery are provided in Appendix 9.***

### 3 SELECTION OF CENTRES/CLINICIANS

#### 3.1.1 Muhimbili University of Health and Allied Sciences (MUHAS)

MUHAS has established in collaboration with the MNH a dedicated HIV clinic that offers comprehensive HIV care. Additionally, a dedicated HIV vaccine clinical trial unit is in place within MNH premises that is closely linked with the Department of Microbiology/Immunology at MUHAS. This allows for an ethical conduct of HIV vaccine trials by providing an experienced study team, community outreach team, pharmacy expertise, data management capabilities, as well as competent laboratories. The HIV vaccine clinic has built up experience and capacities throughout the conduct of the HIVIS03 trial and the ongoing TaMoVac I study. The clinical and laboratory study team is GCP and GCLP trained and repeat training is performed every other year. Throughout these studies good relationships have been established to a cohort among Police Officers which serves as the basis for the recruitment. Extended community involvement into the general population as a source of recruitment has been established throughout the TaMoVac I. The clinical and laboratory study team is GCP/GCLP trained and repeated training is performed every other year. Operators performing the ELISpot assay have received training and passed an operators validation test which involves running three known samples with low, medium and high IFN-gamma ELISpot reactivity to a peptide pool on three different occasions.

#### 3.1.2 NIMR-Mbeya Medical Research Center (MMRC)

MMRC had been involved in past HIV vaccine and cohort trials and has established an experienced study clinic, community outreach team, pharmacy and laboratories. MMRC has built up trial experience throughout numerous past and ongoing HIV cohort (HISIS, CODE, RV217) and HIV vaccine trials (RV172, TaMoVac I and RV262). Clinical support is provided throughout close collaboration with the Mbeya Referral Hospital (MRH). The MMRC labs include a clinical laboratory (haematology, clinical chemistry, serology, CD4 count analysis, HIV testing and HIV RNA) as well as an immunological lab which has established FACScanto flow cytometry, ICS and ELISPOT assays throughout various studies. Both labs have been accredited by the College of American Pathologists (CAP) and participate in external QA/QC programs with UKNequas and CAP and follow therefore the highest standard of quality control and validation which is audited and monitored yearly by independent consultants. The MMRC labs have been recognized as one of the national reference laboratories. The clinical and laboratory study team are GCP/GCLP trained and repeat training is performed every other year.

#### 3.1.3 Centro de Investigação e Treino em Saúde da Polana Caniço (CISPOC), Instituto Nacional de Saúde (INS) in Maputo.

The laboratory at the INS has been improved in terms of needed reagents and equipment to enable screening and safety evaluation (HIV serology, biochemical tests, as well as haematological tests) of potential volunteers as well as monitoring of immune responses following vaccination (Interferon-gamma ELISPOT assay). Local reference values were determined for T-lymphocyte subsets, haematological and biochemical parameters using samples from healthy youths. A new research clinic has been built and equipped to accommodate the TaMoVac trials and other research projects. Personnel have been trained in GLP and GCP and taken a pivotal role in adapting the TaMoVac protocol to local conditions.

Since the end of 2009, a cohort of youths (N=1380) attendees at Hospital Central de Maputo (HCM) have been recruited to assess its suitability for future HIV vaccine trials by determining the prevalence and incidence of sexually transmitted viral infections. Mozambique has a cohort of youths available for HIV vaccine trials. The Youth Clinic at HCM has an established team that works with Youths, and will serve as a base for the cohort of the proposed trial. In preliminary workshops around 200 youths have expressed a general

interest in vaccines. A subset have declared an explicit interest in HIV vaccine trials and been invited to more detailed workshops on HIV vaccines. Those that then express an interest to themselves participate in the planned trial are invited to the clinic for individual information, counselling and eligibility checks. In addition, individuals who attended the Youth Clinic for general services including HIV counselling and testing, STI screening and health education will also be invited to participate in the trial.

## 4 SELECTION OF PARTICIPANTS

There will be **no exceptions** to eligibility requirements at the time of randomisation. Questions about eligibility should be addressed prior to attempting to randomise the participant.

The eligibility criteria for this trial have been carefully considered. The eligibility criteria are the standards used to ensure that only appropriate participants are considered for this study. Participants not meeting the criteria should not join the study. For the safety of the participants it is important that no exceptions be made to these criteria for admission to the study.

Participants will be considered eligible for enrolment in this trial if they fulfil all the inclusion criteria and none of the exclusion criteria as defined below.

### 4.1 Participant inclusion criteria

1. Age: 18 to 40 years
2. Willing to undergo counselling and HIV testing
3. Have a negative antigen/antibody ELISA for HIV infection
4. Able to give informed consent
5. Basic abilities to read and write
6. Satisfactory completion of an assessment of understanding prior to enrolment defined as 90% correct answers after three opportunities to take test
7. Resident in Dar es Salaam, Mbeya or Maputo catchment areas, and willing to remain so for the duration of the study
8. At low risk of HIV infection, defined as the absence of an identifiable risk factor/behaviour according to a risk assessment questionnaire. The following criteria will be considered high risk leading to exclusion:
  - sexual partner with HIV
  - sexual partner with unknown HIV serostatus who is also unwilling to use protective condoms consistently in all sexual relations
  - sexual partner is known to be at high risk for HIV
  - more than two sexual partners in the last 6 months
  - history of being an alcoholic [as medically defined or more than 35 units /week] or intravenous drug abuse or ongoing other chronic drug abuse (e.g. marijuana)
  - history of STI within past 6 months
9. Verbal assurances that adequate birth control measures are used not to conceive/father a child during the study and up to 3 months after the last vaccine injection. Adequate birth control is defined as follows:
  - Contraceptive medications delivered orally, intramuscularly, vaginally, or implanted underneath the skin
  - Surgical methods (hysterectomy or bilateral tubal ligation)
  - Condoms, diaphragms
  - Intrauterine device (IUD)
  - Abstinence
10. Women shall have a negative urinary pregnancy test
11. Be willing to practice safe sex for the duration of the study to avoid sexually transmitted infections including HIV

12. Good health as determined by medical history, physical examination, clinical judgment and by key laboratory parameters as judged by the study physician
13. Laboratory criteria within 8 weeks prior to enrollment:
  - Hb >10.5 g/dl
  - White blood cell count >2000 to <13,000 cells/mm^3
  - Neutrophils >1,100 cells /mm^3
  - Lymphocytes >1.0 cells/mm^3
  - Platelets >125,000/ mm^3
  - Random Blood Glucose <6.44 mmol/L; if elevated, then a Fasting Blood Glucose <6.11 mmol/l
  - Bilirubin <1.1 x uln
  - ALT <1.25 x uln
  - Creatinine <1.1 x uln
  - Urine dipstick for protein and blood: negative or trace. Glucose negative.

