## 4.2 Participant exclusion criteria

The following are the criteria for exclusion from the study:

1. At risk of HIV infection as mentioned above in the inclusion criteria
2. Active tuberculosis or other systemic infectious process elicited by review of systems, physical examination and laboratory detection (for example detection of Hepatitis B surface antigen or active syphilis)
3. A history of immunodeficiency, ongoing medical and/or psychiatric condition and/or chronic illness requiring continuous or frequent medical intervention
4. Autoimmune disease by history and physical examination
5. Hives or recurrent hives and severe eczema
6. Substance abuse problems (including traditional medicine) during the past 12 months that in the opinion of the investigator would preclude participation
7. History of grand-mal epilepsy, or currently taking anti-epileptics
8. Received blood or blood products or immunoglobulins in the past 3 months.
9. Receiving immunosuppressive therapy such as systemic corticosteroids or cancer chemotherapy
10. Use of experimental therapeutic agents within 30 days of study entry
11. Reception of any live, attenuated vaccine within 60 days of study entry. Medically indicated subunit or killed vaccines (e.g., Hepatitis A or Hepatitis B) are not exclusionary but should be given at least 2 weeks before or after HIV immunisation to avoid potential confusion of adverse reactions.
12. History of cardiac disease including:
  - Previous myocardial infarction (heart attack)
  - angina pectoris; congestive heart failure
  - valvular heart disease
  - cardiomyopathy
  - myo/pericarditis
  - stroke or transient ischemic attack
  - chest pain or shortness of breath at rest or with activity (such as walking up stairs)
  - arrhythmia/episodic palpitations (not excluded: sinus arrhythmia)
  - pacemaker or
  - other heart conditions under the care of a doctor

13. Abnormality in ECG that could indicate risk or make interpretation of vaccine effects difficult according to the study operating procedures. ECG with clinically significant findings, or features that would interfere with the assessment of myo/pericarditis, including any of the following:
  - conduction disturbance (complete left or complete right bundle branch block or nonspecific intraventricular conduction disturbance with QRS >120 ms, an AV block grade II or III, or QTc prolongation [ $> 440\text{ms}$ ])
  - significant repolarisation (ST segment or T wave) abnormality

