- 16) That blood tests might include genetic testing. The risks of genetic testing and how to prevent them within the study will be explained.
- 17) That participants can withdraw study participation at any time without any disadvantages.
- 18) Confidentiality and trial surveillance

Upon this information about the trial and the informed consent procedures, consenting volunteers will be requested to successfully pass a test of understanding (**Appendix 4**) with at least 90% of correct answers with the possibility of maximum 3 repeated attempts.

Study personnel will assess volunteers for past and current risk of HIV infection using the Risk Assessment Questionnaire (**Appendix 5**), followed by counselling for those who will consent to undergo HIV test prior to collecting blood. The counselling process will ensure that volunteers have sufficient knowledge about HIV infection to understand what the test is for, the implications of a positive, negative and equivocal result and the standard of care available for HIV infection locally. They will also be informed on how and when they will receive the result.

After written informed consent has been collected, assessments and investigations will be undertaken according to the schedule in **Appendix 2**. These include demographic, sexual and medical histories, general examination, ECG and collection of urine and blood samples for routine laboratory investigations. Screening investigations for sexually transmitted infections including HIV will be collected (**see section 7.2**).

As soon as the medical report is received and all required test results are available:

- data will be entered onto the screening CRFs and the results of the screening investigations will be reviewed and eligibility signed off by a physician
- completed screening CRFs for all volunteers, whether or not they are eligible will be entered onto the trial database.

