## 5 ENROLMENT & RANDOMISATION PROCEDURE

### 5.1 Enrolment

The Enrolment visit (Study Visit 3) will be counted as Week/Day 0 of the study schedule. During the Enrolment Visit confirmation will be made and recorded that the volunteer fulfils all inclusion/exclusion criteria including laboratory results and eligibility criteria using a checklist. If a volunteer is not found to be eligible a Screening Outcome Form will be filled indicating reasons for ineligibility. Enough time has to be planned for the visit so that all questions from the volunteer about the study can be answered or reflected upon. A senior investigator will confirm if the volunteer understands the concepts of the study and will also assess the willingness of the study volunteer to participate. For enrolment the initial screening number will be used as the study number. This means that study numbers may be discontinuous. The participant will then be randomized into one of the Study Groups.

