### 7.2.3 Routine laboratory parameters

Blood collections for routine laboratory parameters will be performed according to **Appendix 2**. Samples will be analysed at:

1. The Department of Microbiology and Immunology, MUHAS in Dar es Salaam, Tanzania.
2. The main laboratories of the NIMR-MMRC in Mbeya Tanzania.
3. The laboratories at INS in Maputo, Mozambique

Peripheral blood will be collected by clinical staff experienced in phlebotomy into the appropriate containers and transported to the local laboratory.

Mid-stream urine will be collected into a sterile container and either tested on site or transported to the local laboratory.

The following parameters will be collected in all participants:

- Hb, total WBC, neutrophils, lymphocytes and platelets
- Creatinine, total and direct bilirubin, ALT and glucose
- Urine alysis using a dipstick for protein and blood
- Urine test to exclude pregnancy for females only

A urine specimen will be sent to the clinical lab for microscopic analysis and validation if abnormal results are seen ( $\geq +1$  for proteins or blood). Results will be graded by a Study Physician as normal, abnormal/clinically insignificant and abnormal/clinically significant.

All lab values will be interpreted according to established MMRC, MUHAS or INS/HCM local reference ranges. Solicited lab values as indicted below for safety assessment will be graded according to the DAIDS Table for Clinical and Lab Criteria for Definitions (**see Appendix 8**). **Any grade 3 and 4 lab value needs to be confirmed by a second test within 48 hours.** In order to harmonize with local reference ranges, the cut-off for Grade I lab toxicity reporting has been modified for neutrophils from  $\leq 1.300$  cells/ $\mu$ l (DAIDS) to  $\leq 1.100$  cells/ $\mu$ l (local values).

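### The lymphocyte entry limit is printed as >1.0 cells/mm³, 350 times below the protocol's own grade 4 bound; the unit of the HIV RNA limit also needs checking

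*Protocol*

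**What the plan says.** Item 13 of section 4.1 lists the laboratory values a volunteer must meet within 8 weeks before enrolment. The lymphocyte line reads "Lymphocytes >1.0 cells/mm"³. The white cell line in the same list and unit reads "White blood cell count >2000 to <13,000 cells/mm"³, and neutrophils and platelets must exceed 1,100 and 125,000 per mm³.

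Section 4 states that "it is important that no exceptions be made to these criteria for admission to the study". Under section 5.1, staff confirm at the enrolment visit that the volunteer "fulfils all inclusion/exclusion criteria including laboratory results and eligibility criteria using a checklist".

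Appendix 8 grades the absolute lymphocyte count of HIV-negative adults as follows: grade 1 is 600–650/mm³, grade 2 is 500–599, grade 3 is 350–499 and grade 4 is below 350.

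Section 6.8 describes how a reactive HIV test is resolved. A participant counts as uninfected if a qualitative PCR is negative for RNA, or if an ultrasensitive quantitative PCR gives fewer than 50 copies/µl. Section 6.8.2 stops further immunisation in anyone found to be infected.

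**The concern.** A limit of one lymphocyte per cubic millimetre does no work. It stands among limits in the thousands in the same unit, and a volunteer with grade 4 lymphopenia passes it. Because waivers are ruled out and eligibility is confirmed against a list, sites can either apply a number that screens out nobody or substitute one the protocol does not contain. Three centres could substitute three different numbers. A physician who declines a volunteer with 400/mm³ could not point to item 13 for support.

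The HIV RNA limit raises a similar question about its unit. If copies/mL was meant, an infected vaccinee tested by quantitative PCR and falling below the printed limit could be reported as not infected and go on receiving injections that section 6.8.2 says must stop. Section 6.8 sends the clinic only an infected or not-infected result, so clinicians would not see the viral load behind it.

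**Working it through.** **Inputs.** Entry limits are from section 4.1, item 13. Grade bands are the adult (for Hb and lymphocytes, HIV-negative) rows of Appendix 8. The local neutrophil cut-off is from section 7.2.3 and the HIV RNA limit from section 6.8.

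**1. Unit conversion.** 1 × 10⁹/L = 10⁹ cells per 10⁶ mm³ = 1,000 cells/mm³. Appendix 8 uses the same conversion: it pairs 350/mm³ with 0.350 × 10⁹/L.

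**2. Lymphocyte limit against the grades.**
- Grade 4 bound ÷ entry limit = 350 ÷ 1.0 = 350.
- Entry limit ÷ top of grade 1 = 1.0 ÷ 650 = 0.0015.

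**3. The lower limits side by side.**

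| Parameter | Entry limit | Grade 1 band | Limit ÷ top of grade 1 | Grade 4 | Limit ÷ grade 4 bound |
|---|---|---|---|---|---|
| Hb (g/dL) | >10.5 | 10.0–10.9 | 10.5/10.9 = 0.96 | <7.0 | 1.5 |
| WBC (/mm³) | >2,000 | 2,000–2,500 | 2,000/2,500 = 0.80 | <1,000 | 2.0 |
| Neutrophils (/mm³) | >1,100 | 1,000–1,300 | 1,100/1,300 = 0.85 | <500 | 2.2 |
| Platelets (/mm³) | >125,000 | 100,000–124,999 | 125,000/124,999 = 1.00 | <25,000 | 5.0 |
| **Lymphocytes (/mm³)** | **>1.0** | **600–650** | **0.0015** | **<350** | **0.003** |

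Against the local grade 1 cut-off of 1,100 in section 7.2.3, the neutrophil ratio is 1.00. The upper limits for bilirubin (1.1 × ULN), ALT (1.25 × ULN) and creatinine (1.1 × ULN) equal the lower edge of their grade 1 bands. None of these seven limits admits grade 2 or worse. The lymphocyte limit admits grades 2, 3 and 4.

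**4. Do the other counts set a floor indirectly?** Take WBC 5,000, neutrophils 4,500 and lymphocytes 300/mm³, which leaves 5,000 − 4,500 − 300 = 200 other cells.
- WBC: 2,000 < 5,000 < 13,000, met.
- Neutrophils: 4,500 > 1,100, met.
- Lymphocytes: 300 > 1.0, met, although 300 < 350 is grade 4.

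So the white cell and neutrophil limits do not make up for the lymphocyte limit.

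**5. What was intended?** If 1.0 × 10⁹/L was meant (assumption), the limit is 1,000/mm³: 1,000/350 = 2.9 times the grade 4 bound and 1,000/650 = 1.54 times the top of grade 1. That is stricter than the neighbouring limits. Appendix 8 therefore shows that the printed figure is wrong without establishing 1,000/mm³ as the right one.

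**6. Could it be a reading artefact?** The neighbouring numbers and the cubed unit are intact. Section 7.2.3 uses a point as a thousands separator for neutrophils, but that habit would not turn 1,000 into 1.0. No other part of the protocol gives a lymphocyte entry limit.

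**7. HIV RNA.** 50 copies/µl × 1,000 µl/mL = 50,000 copies/mL. If copies/mL was meant (assumption), the printed limit is 1,000 times too lenient. Two features of the sentence point that way: the assay is called ultrasensitive, and the qualitative alternative requires a negative result. The protocol gives no assay name, detection limit or other RNA figure to settle it.

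**The case against.** The strongest answer is that item 13 is not the whole entry rule. Item 12 is itself an inclusion criterion, and it requires good health by "clinical judgment and by key laboratory parameters as judged by the study physician"; the no-exceptions clause covers it equally. Section 4.2 excludes "A history of immunodeficiency". Section 4.4 requires the screening results to be reviewed and "eligibility signed off by a physician". Section 7.2.3 has laboratory values read against local reference ranges and solicited values graded, and adds that "Any grade 3 and 4 lab value needs to be confirmed by a second test within 48 hours". Sections 6.2 and 7.1 repeat safety tests at baseline and before each immunisation. A count of 300/mm³ would come before a physician who must certify good health, and the misprint is so plain that nobody is likely to apply it literally. The checklist, SOP and CRF checks are not shown and may already carry the right figure.

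Much of this stands as mitigation. It makes enrolment of a severely lymphopenic volunteer less likely, and nobody can say from the protocol what the checklist contains. But none of these provisions sets a numeric lymphocyte limit for entry, which is what item 13 is there to do. An obvious error still leaves each site to guess the replacement.

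On HIV RNA, the objection is that calling the unit wrong needs an assay limit the protocol does not state. PCR also comes into play only after reactive, discordant or indeterminate results, and section 6.8.1 repeats testing before each vaccination and at weeks 52 and 64. That is fair, and it is why the point is a query. Repeat testing under the same limit would not by itself correct a misclassification.

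**Conclusion.** The lymphocyte limit is wrong as printed: 350 times below the protocol's grade 4 bound, out of line with seven neighbouring limits, and corrected nowhere else. Item 13 therefore sets no working lymphocyte floor. Confidence is high that the figure is wrong. That 1.0 × 10³ cells/mm³ was intended is an inference for the sponsor to confirm.

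The HIV RNA limit of 50 copies/µl equals 50,000 copies/mL. Whether it is 1,000-fold too lenient depends on the assumption that copies/mL was meant, and the possible harm is confined to the quantitative-PCR branch.

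Both points concern eligibility and participant safety and should be fixed. Neither touches alpha, power, sample size or the ITT analysis.

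**What to change.** - **Section 4.1, item 13:** correct the lymphocyte unit, most likely to >1.0 × 10³ cells/mm³ (1.0 × 10⁹/L), after the sponsor confirms the intended value.
- **Section 6.8:** check the HIV RNA unit against the assay's reporting unit and detection limit, correct it (probably to copies/mL), and state the assay limit in the text.
- **Both:** carry the corrected values into the laboratory SOP, the eligibility checklist and the CRF range checks.

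The cost is one sponsor confirmation per value and two unit corrections, repeated in those working documents. Design, sample size and analysis do not change.
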